## Abstract

**Background:**

Seasonal malaria chemoprevention (SMC) is recommended by the World Health Organization for the sub-Sahel region in sub-Saharan Africa for preventing malaria in children 3 months old to younger than 5 years. Since 2016, the Malian National Malaria Control Program has deployed SMC countrywide during its high malaria transmission season at a rate of 4 monthly cycles annually. The standard SMC regimen includes sulfadoxine-pyrimethamine (SP) plus amodiaquine (AQ). Resistance against SP is suspected to be rising across West Africa; therefore, assessing the effectiveness of an alternative antimalarial drug for SMC is needed to provide a second-line regimen when it is ultimately needed. It is not well understood whether SMC effectively prevents malaria in children aged 5 years or older.

**Objective:**

The primary goal of the study is to compare 2 SMC regimens (SP-AQ and dihydroartemisinin-piperaquine [DHA-PQ]) in preventing uncomplicated *Plasmodium falciparum* malaria in children 3 months to 9 years old. Secondly, we will assess the possible use of DHA-PQ as an alternative SMC drug in areas where resistance to SP or AQ may increase following intensive use.

**Methods:**

The study design is a 3-arm cluster-randomized design comparing the SP-AQ and DHA-PQ arms in 2 age groups (younger than 5 years and 5-9 years) and a control group for children aged 5-9 years. Standard SMC (SP-AQ) for children younger than 5 years was provided to the control arm, while SMC with SP-AQ was delivered to children aged 3 months to 9 years (arm 2), and SMC with DHA-PQ will be implemented in study arm 3 for children up to 9 years of age. The study was performed in Mali’s Koulikoro District, a rural area in southwest Mali with historically high malaria transmission rates. The study’s primary outcome is *P falciparum* incidence for 2 SMC regimens in children up to 9 years of age. Should DHA-PQ provide an acceptable alternative to SP-AQ, a plausible second-line prevention option would be available in the event of SP resistance or drug supply shortages. A significant byproduct of this effort included bolstering district health information systems for rapid identification of severe malaria cases.

**Results:**

The study began on July 1, 2019. Through November 2022, a total of 4556 children 3 months old to younger than 5 years were enrolled. Data collection ended in spring 2023, and the findings are expected to be published later in early 2024.

**Conclusions:**

Routine evaluation of antimalarial drugs is needed to establish appropriate SMC age targets. The study goals here may impact public health policy and provide alternative therapies in the event of drug shortages or resistance.

**Trial Registration:**

ClinicalTrials.gov NCT04149106, https://clinicaltrials.gov/ct2/show/NCT04149106

**International Registered Report Identifier (IRRID):**

DERR1-10.2196/51660

## Introduction

Malaria is endemic to south and central Mali, where over 90% of its approximately 17.6 million population is at risk for infection [1]. The disease primarily burdens rural areas that maintain suitable larval habitats and lack access to adequate health care [1]. Malaria transmission is highly seasonal in Mali (length of the transmission periods varies from 3 to 6 months), with a peak of malaria cases at the end of the rainy season (October through November), though it may be affected by irrigation schemes [2,3]. Deaths due to malaria registered at health centers totaled 1050 in 2017, with 669 (63.7%) occurring among children younger than 5 years. However, these results are likely substantially underreported. For instance, in 2015, health facilities in Mali reported over 2.3 million confirmed malaria cases and 1544 malaria deaths, but actual estimates were 7.5 million and 21,000, respectively [1].

Since 2007, support from the US Presidential Malaria Initiative program and other sponsors resulted in a 50% reduction in Mali’s malaria burden. These efforts have been carried out through increased preventive and treatment measures such as long-lasting insecticide-treated mosquito nets (LLINs), indoor residual spraying, artemisinin-based combination therapies (ACTs), and intermittent preventive treatment of pregnant women (IPTp); and more recently, seasonal malaria chemoprevention (SMC). The most widely implemented malaria control interventions are the joint use of LLINs and rapid treatment of malaria cases with ACTs, IPTp, and SMC. Indoor residual spraying was previously implemented on a small scale in several Malian districts but is currently implemented in only a single district in central Mali.

Despite the broad deployment of these interventions, malaria prevalence and incidence rates remain high in Mali according to the routine Malaria Indicators Surveys [4]. Since 2010, the International Centers of Excellence in Malaria Research (ICEMR), in collaboration with Mali’s National Malaria Control Program (NMCP), has identified significant constraints to malaria control implementation strategies in Mali, including the upward shift of the prevalence of infection and incidence of disease in children younger than 5 years to children aged 5-9 and 10-14 years [5,6]. These findings are particularly significant as the World Health Organization (WHO) guidelines recommend SMC only for children 3 months old to younger than 5 years. Therefore, the Mali NMCP and its partners have expressed SMC effectiveness and intervention strategies as key research priorities.

While the sulfadoxin and pyrimethamine regimen (SP) remains effective in West Africa, resistance to this regimen has been observed in East African regions where *Plasmodium falciparum* is highly prevalent. SMC is not currently recommended for countries in southern and eastern Africa due to widespread resistance, although there are some locations where transmission patterns suggest potential suitability [7,8]. In western parts of Africa, higher frequencies of the triple dihydrofolate reductase mutants and the quadruple mutant (triple dihydrofolate reductase plus dihydropteroate synthetase 437) associated with significant resistance to SP have been observed in children receiving SMC in both Mali and Senegal [9,10]. Recent studies have also reported SP resistance in several parts of Mali [11,12]. The wide-scale deployment of SMC in sub-Saharan African countries required increased focus on *P falciparum* resistance as well as ongoing assessments of new alternative drug combinations for SMC as this strategy has proven to be effective in reducing the impact on severe malaria and mortality in children 3 months old to younger than 5 years [13]. A recent study in Burkina Faso suggests that higher dosages and extended dosing of dihydroartemisinin-piperaquine (DHA-PQ) to 4 monthly doses (and cover the entire high malaria transmission period) could reduce malaria incidence up to 58% during the peak transmission season [14,15]. DHA-PQ has demonstrated excellent efficacy for chemoprevention and benefits from the long half-life of piperaquine and offers a protective efficacy of 98% against malaria in Thai adults when administered monthly [7]. In Senegalese children, similar monthly malaria incidence was observed among children receiving monthly DHA-PQ vs SP+amodiaquine (AQ) as SMC regimen [8].

A study in Uganda reported a 58% greater protective efficacy for DHA-PQ over SP-AQ based on monthly administration among children younger than 5 years [9]. This study aims to determine whether SMC effectively prevents malaria in children aged 5-9 years. The evidence-based approaches used will guide policy in Mali and other countries in West Africa using SMC.

## Methods

### Ethical Considerations

The study was approved by the University of Sciences, Techniques and Technologies Ethics Board under the following reference (N°2019/04/CE/FMPOS). The trial will report the efficacy of 2 SMC subtypes (SP-AQ and DHA-PQ) for preventing *P falciparum* malaria in children aged 5-9 years in Mali. Should the findings show that SMC is efficacious for children in this age group, it may impact policy SMC delivery in Mali.

### Study Site

Mali’s Koulikoro District is situated in its southern region, approximately 50 miles (18 km) north of Bamako and 255 miles (410 km) from the Guinea border [11]. The district maintains 21 health zones and 71 community health posts. The current population in the district is 282,570, with approximately 4% of its population <1 year of age and 18% between 1 and 4 years of age. The total number of villages a community health center covers ranges from 8 to 31. The most populous village is Kolebougou, with 34,712 persons; the least populated is Souban Village, with 5085 persons. Ongoing malaria control activities include case management (rapid diagnostic tests and ACTs), IPTp, SMC, and LLIN use. District health centers maintain clinical and laboratory research capacity and full-time staff and clinicians for malaria screening and patient care. The site was chosen for the proposed research because of its diverse range of malaria control interventions, collaborative research agreements with the University of Sciences, Techniques and Technologies of Bamako, Mali (USTTB), high malaria transmission rates, and rural location.

### Study Design and Population

The study was as a 3-arm cluster-randomized design, as illustrated in Figure 1.

**Figure 1 figure1:**
[figure not shown]
Study design of a 3-arm cluster-randomized trial on age targets for season malaria chemoprevention. The study was performed from July 2019 to March 2023. AQ: amodiaquine; DHA: dihydroartemisinin; PQ: piperaquine; SP: sulfadoxine-pyrimethamine.

The study population includes children aged 3 months to 9 years in each village. Each study arm includes 3 corresponding public health units (PHUs) that differ with respect to their ecology, proximity to the Niger River, and region in the context of Koulikoro District (northern, central, and southern).

### Cluster Selection

A total of 9 villages were randomly selected from Mali’s Koulikoro District for participation. The selection strategy focused on 3 aspects: proximity to the Niger River (which lies in the southern part of the region) and the central and northern parts of the sampling region. Within these strata, villages were rank-ordered according to their populations. Random selection was carried out such that villages of high, medium, and low populations were sampled from each of these strata. A total of 3 villages (1 village per stratum with different ranking in terms of population size) were assigned to a single treatment arm (Figure 2).

**Figure 2 figure2:**
[figure not shown]
Map of the 9 study sites in Mali’s Koulikoro District. The 9 study sites are near the central part of Mali’s Koulikoro District. Study sites were selected as 3 villages near the Niger River, 3 villages in the northern part of Koulikoro District, and 3 villages in the central part of Koulikoro. AQ: amodiaquine; DHA: dihydroartemisinin; PQ: piperaquine; SP: sulfadoxine-pyrimethamine.

The southernmost villages (Gouni, Kenenkoun, Kamani) are situated near the Niger River, while the remaining villages (Doumba, Sinzani, Koula; and Sirakorola, Monzombala, and Chola) lie in the northern and southern parts of the region above the Niger River, respectively.

### Randomization

Probability proportional to population size sampling was used for allocating villages to the study arm. Random treatment assignment was balanced according to population size in each stratum (low, medium, and high), resulting in a 3 by 3 Latin square arrangement (Table 1).

**Table 1 table1:** Study site classification per sampling region within the Koulikoro District, Mali.

Region	Population size		
	Small	Medium	Large
South	Gouni (A)^a^	Kamani (C)	Kenenkoun (B)
Central	Sinzani (B)	Doumba (A)	Koula (C)
North	Chola (C)	Monzombala (B)	Sirakorola (A)

^a^A, B, and C denote the 3 study arms.

Specifically, PHUs were rank-ordered according to their total populations, and the top 3 PHUs (in terms of their populations) were chosen to represent Koulikoro’s southern, central, and northern regions. The PHUs were then randomized to treatment according to the Latin square arrangement shown in Table 1.

### Eligibility and Enrollment

Participants were eligible to participate if they were residents of the sampled village, aged 3 months to 9 years of age at enrollment, were asymptomatic of current chronic diseases, and did not have a history of allergies to SP, AQ, or DHA-PQ therapies. Informed, written consent is required for all study participants annually. Consent was administered in oral or written formats and included a full description of voluntary participation, the right to withdraw from the study at any time, and the right to refuse to answer any question or participate in any research component.

### Study Outcomes

The primary study outcome is the incidence of severe or uncomplicated *P falciparum* malaria. The population denominator for incidence calculations was derived from the house-to-house enumeration with household member listing. Secondary outcomes were abstracted from censuses and enumeration lists for selected villages, including village-level distributions on populations, age, gender, residential status, and LLIN use. Exhaustive selection was carried out in villages for selected PHUs for those children who met the eligibility criteria and for whom consent of parents or tutors for enrollment was obtained. A baseline malaria infection prevalence survey was carried out before the initial SMC campaign. Follow-up surveys at community health centers were also carried out to assess malaria incidence among study participants. Monthly SMC administration and compliance with treatment assessment were captured via reports by caregivers and measurement of AQ metabolite by enzyme-linked immunosorbent assays. Demographic data, including age, sex, and clinical parameters (including temperature, pulse, and respiration rate), were recorded at a community health center visit. Malaria cases were defined as fever or a history of fever within the past 48 hours associated with either positive malaria rapid diagnostic test or a positive blood smear prepared during that visit.

### Hypotheses and Rationale

The primary hypotheses were as follows:

Malaria incidence in children was at least 10% higher in the 5- to 9-year age group without SP-AQ than in children in the 5- to 9-year age group with SP-AQ.Malaria incidence in children 3 months old to younger than 5 years receiving DHA-PQ was not statistically different from children in the same age group receiving SP-AQ.

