### A Priori Sample Size and Statistical Power

The power and sample size assessment is based on the ability to detect a clinically significant difference in malaria incidence proportions between the 3 comparison groups in year 1. The minimum clinically meaningful differences between the comparison groups was set at 10%. The sample sizes were calculated assuming a design effect of 2 with a 2-sided type I error set at 0.05 and power set at 80%. The number of required subjects per study arm for detecting at least 10% differences in malaria incidence proportions was 1552 in year 1. This result was inflated by 233 subjects in year 2 to account for new subjects due to increased child ages, yielding 1785 participants per arm total or 5355 participants overall.

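### Primary hypothesis 2 is worded as a non-significant difference between DHA-PQ and SP-AQ, which cannot support the intended claim that DHA-PQ is an acceptable alternative

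*Protocol article*

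**What the plan says.** Under Hypotheses and Rationale, the article lists two primary hypotheses. The first carries a quantity: incidence at least 10% higher in 5- to 9-year-olds without SP-AQ. The second carries none. It says that incidence in children from 3 months to under 5 years "receiving DHA-PQ was not statistically different from children in the same age group receiving SP-AQ".

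The use of the comparison is stated elsewhere. The Abstract's Objective says "we will assess the possible use of DHA-PQ as an alternative SMC drug in areas where resistance to SP or AQ may increase". The Abstract's Methods adds: "Should DHA-PQ provide an acceptable alternative to SP-AQ, a plausible second-line prevention option would be available". The Discussion again presents DHA-PQ as an alternative in the event of resistance or supply shortage.

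A Priori Sample Size and Statistical Power is framed as superiority. The assessment is "based on the ability to detect a clinically significant difference in malaria incidence proportions between the 3 comparison groups in year 1", and "The minimum clinically meaningful differences between the comparison groups was set at 10"%. The article does not connect that 10% to hypothesis 2 as a margin, and it contains no equivalence or non-inferiority test and no confidence-interval rule.

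**The concern.** To call DHA-PQ an acceptable alternative is to say that it is not worse than SP-AQ by more than some tolerable amount. The hypothesis as worded is met whenever a test of no difference fails to reject. The two are different statements. A noisier comparison makes non-significance more likely, so the less the trial can tell us, the easier the hypothesis is to confirm.

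The error that matters for policy is accepting a regimen that protects young children less well. Under this wording, the chance of that error is whatever the type II error happens to be at the true difference. It is not held at a chosen level.

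This is not a detail left to an analysis plan. The article states the criterion, and a margin added elsewhere would replace the published primary hypothesis rather than complete it.

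**Working it through.** **1. Reproduce the planned size.** The article states: "The number of required subjects per study arm for detecting at least 10% differences in malaria incidence proportions was 1552 in year 1", "assuming a design effect of 2 with a 2-sided type I error set at 0.05 and power set at 80"%. It gives no baseline incidence. Taking 50% v 40%:

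n = [1.960·√(2·0.45·0.55) + 0.842·√(0.5·0.5 + 0.4·0.6)]² / 0.10² = 387.3, so 388.

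388 × 2 (design effect) × 2 (age groups) = 1552, an exact match. The rest follows: 1552 × 0.15 = 233 and 1552 + 233 = 1785, then 3 × 1785 = 5355, as in "yielding 1785 participants per arm total or 5355 participants overall".

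The 50% baseline, the doubling for age groups and the reading of 10% as percentage points are assumptions. The match is not unique. With a relative 10% reduction and design effect 2, the requirement falls from 2136 at a 60% baseline to 1426 at 70%, so it passes through 1552 in between.

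**2. Inputs for the illustration (9-village phase only).** Assumed: 776 under-5s per arm (half of 1552), effective size 776 / 2 = 388, and SP-AQ incidence of 20–50%. There are 3 villages per arm (Discussion). Under-5s receive SP-AQ in two of the three arms (Abstract, Methods), so the comparison is either 3 v 3 villages (4 df) or 6 v 3 villages (7 df).

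**3. Chance of a non-significant result when DHA-PQ is worse by d.** SE = √[p(1−p)/n₁ + (p+d)(1−p−d)/388], with n₁ = 388 (one SP-AQ arm) or 776 (both). Normal test: Φ(1.960 − d/SE), since the opposite tail is negligible. The t-test uses the noncentral t with noncentrality d/SE.

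Worked at p = 40%, d = 10 points:
- One arm: SE = √(0.49/388) = 0.0355 and d/SE = 2.81. Non-significant: 19.7% (normal), 43.2% (4 df).
- Both arms: SE = √(0.24/776 + 0.25/388) = 0.0309 and d/SE = 3.24. Non-significant: 10.1% (normal), 20.7% (7 df).

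Across incidences of 20–50%:

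| True deficit | One SP-AQ arm: normal | One arm: t, 4 df | Both arms: normal | Both arms: t, 7 df |
|---|---|---|---|---|
| 10 points | 10–20% | 32–43% | 4.5–10% | 12–21% |
| 5 points | 61–71% | 75–81% | 52–64% | 62–71% |

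A non-inferiority test at one-sided 2.5% accepts a regimen lying exactly at the margin 2.5% of the time.

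**4. Sensitivity.** Design effect 2 with 776/3 ≈ 259 children per village implies an ICC of 1/(259 − 1) ≈ 0.004. At an assumed ICC of 0.01 and 40% incidence, a 10-point deficit against one arm is non-significant in 45% (normal) or 64% (4 df). In the other direction, if all 1552 per arm counted (effective 776), the normal-test figures against one arm fall to 0.5–2% at 10 points and 35–50% at 5 points. That is generous, because an arm's children span both age groups.

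**5. Power of a non-inferiority test.** With a 10-point margin, no true difference and the same inputs, power is Φ(0.10/SE − 1.960). At 40% against one arm, SE = √(2·0.4·0.6/388) = 0.0352, giving 81% (normal) and 58% (4 df). Over incidences of 30–50%, it is 80–86% (normal) or 56–63% (4 df) against one arm, and 79–85% (7 df) against both.

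**The case against.** The strongest reply is that the article states a hypothesis, not a decision rule. Nowhere does it say that a non-significant test will establish acceptability. A reader might infer an explicit rule, but the text does not support that. The rule comes from reading the hypothesis together with the stated objective. It is the natural reading of a primary hypothesis, but it remains an inference.

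A reader might also infer that the risk of adopting a worse regimen is entirely uncontrolled. That goes too far. The sample size section sets 80% power for a 10% difference, so the risk of missing a deficit of that size is nominally 20%. This is laxer than 2.5%, but it is a stated level. The high rates occur at 5 points, which is below what the protocol calls meaningful and inside the largest margin proposed here.

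Third, it is tempting to quote only the 3 v 3 village figures (43% and 81% at 40% incidence). The hypothesis compares DHA-PQ with children of the same age receiving SP-AQ, which can cover two arms. Pooling them roughly halves the 10-point figures.

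Fourth, all of these rates describe the 9 villages, which the Discussion says may be regarded as a pilot. Phase 2 randomizes health posts across the whole district, 71 in all, and may have far more power.

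These replies limit the size of the problem. None of them turns a non-significant difference into evidence of similarity.

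**Conclusion.** The wording of hypothesis 2 does not fit the claim that it is meant to support, and nothing else in the article repairs it. That conclusion needs no assumed figures.

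The size is less certain. It rests on an assumed incidence, an assumed 776 under-5s per arm, the protocol's design effect of 2, and the choice between one and two SP-AQ arms as comparator. Within those assumptions, and for the 9-village phase only, a regimen worse by 10 points would pass as non-significant somewhere between about 4.5% and 43% of the time, against 2.5% under a non-inferiority test. The article gives no sample size for the 71-post phase, so no rate can be given for the whole trial.

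**What to change.** Restate hypothesis 2 as non-inferiority of DHA-PQ to SP-AQ in children under 5:

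- Conclude non-inferiority only if the upper limit of the cluster-adjusted two-sided 95% confidence interval for the incidence difference (DHA-PQ minus SP-AQ) lies below a fixed margin. The margin should be no larger than the 10% in the sample size section, read as percentage points.
- State whether the comparator is one SP-AQ arm or both.
- If the criterion is not met, report the estimate and interval as inconclusive, not as showing no difference.
- Show the result in both the intention-to-treat and per-protocol analyses that the Results section already plans.

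The change is to wording and inference, but it has a price. The claim becomes harder to make: with a 10-point margin and 30–50% incidence, power against one SP-AQ arm is 80–86% by the normal approximation but only 56–63% with 4 df. Using both arms brings it to about 79–85% with 7 df. A tighter margin would not be met by the 9-village phase: 5 points would need about 2010–3140 under-5s per arm (80% power, normal approximation, design effect 2, incidence 20–50%).

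The Results section says that data collection has ended and preliminary findings have been published. The report should therefore say that the margin was fixed afterwards and is anchored to the pre-stated 10%.
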